**Figure 1 F1:**
[figure not shown]
**Trial Flow chart**.

Patients enrolled in the conservative management arm will be followed up twice weekly by Electronic Fetal Heart Rate monitoring and Biophysical profile (Figure 1). Patients will be followed up until 41+0 gestational weeks. Women, who will not deliver by this gestational age, will be admitted for labour induction (see the protocol above). Induction of labour will be offered when non-reassuring fetal status is suspected. All patients in the conservative arm will undergo fetal weight ultrasound estimation prior to induction. Patients with estimated fetal weight over 4000 gr will be offered a caesarean section.

General information on recruited patients, outcomes and randomization group will be indicated in an appropriate paper questionnaire in the first instance and then reported on an electronic database accessible from different study sites in the second instance. In each participating centre, medical personnel will fill up the electronic form directly. Data will be kept anonymous and will be analyzed by the Epidemiology and Biostatistics Unit - IRCCS Burlo Garofolo, using STATA 9 statistical package. Continuous variables will be reported as mean and standard deviation, categorical variables as proportions and percentages. The two groups will be compared by their main characteristics to evaluate the efficacy of the randomization process. To evaluate the main outcome of the study, C-section incidence will be compared between the two groups using the χ^2 ^test. Possible confounders such as: blood glucose control, obesity, participating centre policy etc. will be controlled through multivariate analysis (logistic regression). To compare secondary outcome variables between the two groups, the ANOVA technique will be used for continuous variables and χ^2 ^test for categorical. Statistically significant differences will be determined by a p-value inferior to 0.05. Although crossovers between the two allocation groups could complicate data interpretation, it is impossible to prevent them. However, data will be analysed by intention-to-treat. Finally, a sensitivity analysis will be carried out to confirm that results do not change significantly despite the variety of populations included in the study.

Data will be monitored by The Epidemiology and Biostatistics Unit at The Institute for Maternal and Child Health - IRCCS Burlo Garofolo. Serious adverse events will be reported to an apposite committee. This will consist of three senior obstetricians working at different recruiting centres who will independently verify that the adverse outcome has occurred, through assessing the patient's record. The Steering Committee for this trial will comprise [name] (as chairman), [name] and [name].

Ethical approval of the protocol was obtained by Burlo Garofolo Ethical Committee (Coordinating Centre). Approval at each participating centre is required before starting the recruitment process and application for approval at each local Ethical Committee will take place in the next few months. The procedure will be explained in detail to recruited patients, who will be provided an information sheet and finally asked to sign a consent form if willing to participate.

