## Methods/Design

The proposed research regards a multicentre open label randomized controlled trial in women with GDM between 38+0 and 39+0 gestational weeks. The study will be carried out by the GINEXMAL Study Cooperative Research Group including 9 Teaching Hospitals, 5 in Italy and 4 abroad. The Institute for Maternal and Child Health - IRCCS Burlo Garofolo (Italy) together with The Helen Schneider's Hospital for Women - Rabin Medical Centre (Israel) will be the coordinating centre of the research project.

A total sample of 1760 patients (N = 880 per intervention group) will be recruited. The sample size has been estimated to be sufficiently large to achieve significant results with concerns to the main outcome of the study. In particular, it will be able to demonstrate a difference between the two arms ≥ 6% (31% of C-section in the expectant group and 25% in the induction group; relative difference between the 2 groups equal to 20% in favour of induction [13]), considering α error equal to 5% and 80% power.

Randomization will be centralized and coordinated by the Epidemiology and Biostatistics Unit (IRCCS Burlo Garofolo, Italy) using a computer-based method. The randomization list will be blocked (using blocks with a size of 10) and stratified by centre. The allocation concealment will be guaranteed through the use of closed opaque envelopes, consecutively numbered. In each envelope a patient's allocation group will be indicated, based on randomization. The study will be an open label trial because of the practical impossibility to blind either health professionals or patients to the allocation group.

Medical personnel directly involved in the management of the patient, will open the first available envelope and assign the patient to the corresponding randomization group (experimental group: induction of labour or control group: expectant management). The recruitment phase of the study will last 2 years.

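### The primary χ² test ignores the centre stratification of the randomisation, so it is slightly conservative if C-section rates differ between centres; planned power is kept

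*Protocol article*

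**What the plan says.** **Randomisation** (protocol article, Methods/Design): "The randomization list will be blocked (using blocks with a size of 10) and stratified by centre". The study group is described as "9 Teaching Hospitals, 5 in Italy and 4 abroad".

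**Primary test** (Methods/Design, analysis paragraph after Figure 1): "C-section incidence will be compared between the two groups", by a χ² test. No stratification is mentioned.

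**Adjustment** (next sentence): "Possible confounders such as: blood glucose control, obesity, participating centre policy etc. will be controlled through multivariate analysis (logistic regression"). The list is open-ended, and the model is not named as the primary analysis. The paragraph ends with a sensitivity analysis prompted by the variety of populations in the study.

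**Design figures** (Methods/Design): "31% of C-section in the expectant group and 25% in the induction group", "considering α error equal to 5% and 80% power", with 880 women per arm.

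**The concern.** Blocking within centre balances the arms at each hospital, so differences between hospitals largely cancel out of the treatment comparison. A plain χ² takes its variance from the pooled rate, as if the women came from one population, and so still counts those differences as noise. Its standard error is then larger than the real sampling variation of the estimate, and the test rejects too seldom.

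The article gives reasons to think that centre rates may differ. It names centre policy as something to control, acknowledges varied populations, and leaves the next step after failed cervical ripening, including C-section, to local protocols. At stake are the calibration of the main p-value and a little efficiency. There is also the question of which result governs if the crude and centre-adjusted analyses fall on opposite sides of 0.05.

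**Working it through.** **1. Inputs from the article.** Rates 0.31 and 0.25, difference 0.06, α 5% (taken as two-sided, which reproduces the sample size), power 80%, 880 per arm, 9 centres.

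**2. The plan's own figure.** With mean rate p̄ = 0.28,

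n = [1.96·√(2·p̄(1−p̄)) + 0.842·√(pE(1−pE) + pI(1−pI))]² / 0.06²

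= [1.96·√0.4032 + 0.842·√0.4014]² / 0.0036 ≈ 878 per arm, against 880 stated. Power at 880 is 80.1%. The sample size is sound.

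**3. Assumptions.** The article gives no centre-specific rates, so the spread is assumed: 9 equal centres, arms balanced within centre, centre log-odds spread as normal quantiles with the same SD in both arms, and average rates held at 31% and 25%. A log-odds SD of 0.3 gives expectant-arm centre rates of 21–42%; an SD of 0.5 gives 15–50%.

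**4. Standard errors in closed form.** For a set of centres, the average within-centre variance is the pooled p(1−p) minus the between-centre variance of the rates.

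- Crude SE: √(2·0.2016/880) = 0.02141, whatever the spread.
- 21–42%: the SD of the centre rates is 0.063 (expectant), 0.056 (induction) and 0.059 (mean of the arms). Stratified SE = √(2·(0.2016 − 0.059²)/880) = 0.02122. Actual SD of the difference = √((0.4014 − 0.063² − 0.056²)/880) = 0.02117. Crude over actual = 1.011.
- 15–50%: the SDs are 0.103, 0.091 and 0.097. Stratified SE = 0.02090; actual SD = 0.02085; crude over actual = 1.027.

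About 0.2% of each excess comes from pooling the two arms' rates (0.02141/0.02136 with identical centres), not from centre.

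**5. Power in closed form,** Φ[(0.06 − 1.96·SE)/actual SD].

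- 21–42%: crude Φ(0.01804/0.02117) = 80.3%; stratified Φ(0.01841/0.02117) = 80.8%.
- 15–50%: crude Φ(0.01804/0.02085) = 80.7%; stratified Φ(0.01904/0.02085) = 81.9%.

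**6. Type I error in closed form,** both arms at 31% on average.

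- 21–42%: SE ratio √(0.2139/(0.2139 − 0.063²)) = 1.009, which gives a two-sided error of 4.8%.
- 15–50%: ratio √(0.2139/(0.2139 − 0.103²)) = 1.026, which gives 4.4%.

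**7. Simulation,** 200,000 trials per scenario, crude χ² against the centre-stratified Mantel-Haenszel test:

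| Assumed expectant-arm centre rates | Crude SE too wide by | Crude type I error | Crude power | Stratified power |
|---|---|---|---|---|
| all 31% | 0% | about 5.0% | 80.0% | 80.0% |
| 21–42% | 1.2% | 4.7% | 80.4% | 80.9% |
| 15–50% | 2.7% | 4.4% | 80.9% | 82.2% |
| 9–61% | 6.3% | 3.8% | 81.4% | 84.4% |
| 6–68% | 9.2% | 3.2% | 82.2% | 86.4% |

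The stratified test's type I error stays at about 5% throughout (4.9–5.1%). The closed-form and simulated values agree closely. The last two rows are extreme spreads, shown only to bound the effect.

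**The case against.** The strongest defence is that nothing promised is lost. The crude test reaches 80% power in every row, and its power rises slightly with heterogeneity because the true sampling variation shrinks. A reader might infer that the trial falls short of its planned power. It does not: the loss is only relative to a stratified test. Nor is false-positive risk inflated, since the error is on the conservative side. Both points stand.

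Second, the size depends on an assumed spread. Uniform eligibility (no prior C-section, no estimated fetal weight above 4000 g, no contraindication to vaginal delivery) narrows the scope for centre differences. The local-protocol clause concerns only women whose cervix has not ripened after five prostaglandin attempts. This also stands, so the moderate rows are the ones to weigh.

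Third, centre is not ignored. The logistic regression sentence directly follows the main test and can be read as part of the main-outcome analysis, and a sensitivity analysis for varied populations is planned. This stands in part. An adjusted result may well exist, but the article does not name it as the deciding test. It lists centre policy as a possible confounder although stratified blocking already balances centre between the arms. The reason to include centre is to match the variance to the design.

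Finally, a reader might extend the point to a faulty confidence interval or a wrong effect scale because the model named is logistic. The article specifies no interval for the main outcome, and a condensed article may leave effect measures to the full plan, so neither criticism is supported.

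**Conclusion.** The mismatch between a centre-stratified randomisation and an unstratified primary test is explicit in the article. Its consequence is small: for moderate to fairly wide assumed centre differences, a standard error about 1–3% too wide, a type I error of 4.4–4.7%, and 0.5 to 1.3 percentage points less power than a stratified test. It is zero if centres are alike. The mechanism and its direction are certain. The size rests on the assumed spread of centre rates, equal centre sizes and balance within centre. This is a weakness of efficiency and calibration; the planned test remains valid and keeps its planned power.

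**What to change.** In the analysis paragraph, name a Mantel-Haenszel test stratified by centre as the primary analysis of C-section, with the matching centre-stratified risk difference as the estimate. Keep the crude χ² as a sensitivity check. Fixing this before outcome data are seen also settles which result governs if the analyses disagree.

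The cost is one sentence. Centre is already recorded for randomisation, the sample size need not change, and no power is lost if centres turn out alike. With arms balanced within centre, the stratified and crude risk differences will be nearly equal; what changes is mainly the standard error.

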**Exclusion Criteria**

Pre-GDM
Prior C-section
Suspected estimated foetal weight > 4000 g at enrolment
Any known contraindications to vaginal delivery
Uncertain gestational age
Non reassuring foetal wellbeing necessitating delivery
Maternal pregnancy-related disease necessitating delivery
Bishop score > 7 at enrolment
Known foetal anomaly

If there are no other contraindications to deliver vaginally, patients will be enrolled between 38+0 and 39+0 weeks of gestational age (verified by last menstrual period (LMP) and confirmed by first trimester ultrasound). In the case of a discrepancy, gestational age assessed by ultrasound in the first trimester will be considered as the true reference. Uncertain gestational age or any major fetal anomaly will cause exclusion from the trial (Table 1). Women diagnosed with pre-gestational diabetes or demonstrating a prior C-section in their obstetrical history will be excluded. The identification of non-reassuring fetal status assessed by cardiotocography alone or as a formal part of a biophysical profile [22] or the presence of maternal or fetal conditions complicating pregnancy (e.g. severe preeclampsia/HELLP Syndrome or severe fetal growth restriction) and requiring immediate obstetrical intervention (prompt delivery or prompt C-section) will lead to the patient's exclusion.

After careful evaluation of inclusion and exclusion criteria (Table 1), suitable patients will have been identified. On the day of enrolment, an ultrasound assessment of fetal weight, as well as a Bishop score evaluation, will be performed. Whenever the estimated fetal weight exceeds 4000 gr, patients will be excluded from the trial and offered a C-section. A Bishop score greater than 7 will automatically exclude the patient from the trial. Furthermore, an attentive evaluation of possible contraindications to vaginal delivery and an assessment of fetal wellbeing through a cardiotocographic trace will be carried out at enrolment. The remaining inclusion/exclusion criteria will be assessed through the evaluation of the patient's current and past obstetric records.

Eligible women will be provided a comprehensive explanation of the project by the obstetrician on call, in terms of study procedures and risks versus benefits attached. Patients wishing to take part will be asked to sign a written consent form before being allocated to the randomization group.

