Secondary outcomes of the study will be assessed at time of delivery and/or during maternal and neonatal admission until discharge. Outcomes evaluated at delivery are: gestational age, mode of delivery (spontaneous or operative vaginal delivery, C-section), spontaneous or instrumental third stage of labour, presence of perineal tears or performance of an episiotomy, postpartum haemorrhage (defined as bleeding from the genital tract of 1000 ml or more in the first 24 hours following the delivery of the baby) [20]. Furthermore, the occurrence of shoulder dystocia, defined as a delivery that requires additional obstetric manoeuvres to release the shoulders after gentle downward traction has failed, will be evaluated [24]. Shoulder dystocia occurs when either the anterior or, less commonly, the posterior fetal shoulder impacts on the maternal symphysis or sacral promontory [24] and its diagnosis will be confirmed by an apposite committee for serious adverse events. Serious adverse outcomes such as shoulder dystocia, fourth-degree perineal tears and uterine rupture will be reported to an independent data monitoring committee. Finally, the eventual manoeuvres performed to disengage the shoulder, newborn's birth weight, Apgar score at 1', 5' and 10' minutes, occurrence of arterial cord pH inferior to 7.02 will be recorded and evaluated.

The remaining secondary outcomes will be assessed until maternal and fetal discharge and are as follows: need for blood transfusion (whose main determinant should be the clinical picture and whose main therapeutic goals are to maintain haemoglobin > 8 g/dl, platelet count > 75 × 109/l, prothrombin < 1.5 × mean control, activated prothrombin times < 1.5 × mean control, fibrinogen > 1.0 g/l, when used in the most appropriate combination of intravenous clear fluids and blood products) [25], maternal or neonatal intensive care unit admission, duration and diagnosis, neonatal birth trauma (Erb's palsy, bone fracture, intra-cerebral/intra-ventricular haemorrhage, subdural hematoma), neonatal respiratory distress/transient tachypnea, neonatal need for respiratory support, neonatal hyperbilirubinemia, polycythemia or hypoglycaemia and maternal and perinatal death.

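### Birth weight is compared without adjusting for the fetal weight estimated before allocation; ANCOVA would be a free gain in precision

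*Protocol article*

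**What the plan says.** Three parts of the Protocol article bear on this.

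- **Method** (Methods/Design, analysis paragraph after Figure 1): for secondary outcomes, "the ANOVA technique will be used for continuous variables". No covariate or further factor is named. With two groups, the natural reading is an unadjusted comparison of means. The only covariate adjustment described is a logistic regression for possible confounders. It follows the C-section comparison, cannot be fitted to a continuous outcome, and does not list fetal weight among its examples.
- **Outcome** (Discussion, list of secondary outcomes): among the items recorded at delivery are "newborn's birth weight, Apgar score at 1', 5' and 10' minutes".
- **Baseline measurement** (text under Exclusion Criteria): "On the day of enrolment, an ultrasound assessment of fetal weight, as well as a Bishop score evaluation, will be performed". The result is used at once: "Whenever the estimated fetal weight exceeds 4000 gr, patients will be excluded from the trial and offered a C-section". Because the estimate decides eligibility, it comes before allocation.

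The planned size is given in Methods/Design: "A total sample of 1760 patients (N = 880 per intervention group) will be recruited".

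**The concern.** The enrolment scan estimates the quantity that is later weighed at birth. Women enter between 38+0 and 39+0 weeks, and the expectant arm is followed to 41+0 before admission for induction, so the gap between scan and birth is at most about three weeks. A baseline value of this kind usually explains part of the variation between babies. An analysis that omits it leaves that variation in the error term.

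What is at stake is the width of one confidence interval. Birth weight is a secondary outcome, and the trial is neither sized on it nor decided by it. It is still of interest in a trial whose rationale includes fetal growth under expectant management, and the extra information comes from a scan that the protocol already requires.

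**Working it through.** **Inputs from the document:** 880 women per arm, 1:1 allocation; C-section rates of 31% and 25%; α 5%; power 80%.

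**Assumed inputs, not in the document:** birth weight SD of 450 g (range 400 to 500 g); within-arm correlation r between enrolment estimate and birth weight of 0.3 to 0.7.

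**Step 1: the plan's own figure.** There is no figure for birth weight, so the check is on the stated sample size. For two proportions with a two-sided test and pooled variance under the null:

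n = [1.96·√(2 × 0.28 × 0.72) + 0.8416·√(0.31 × 0.69 + 0.25 × 0.75)]² / 0.06² = (1.2445 + 0.5332)² / 0.0036 ≈ 878 per arm.

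This agrees with 880; power at 880 is 80.1%. The sample size is sound, and nothing below changes it.

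**Step 2: unadjusted birth weight comparison.** SE = 450·√(2/880) = 21.5 g. The 95% half-width is 1.96 × SE = 42.0 g (37.4 g at SD 400; 46.7 g at SD 500).

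**Step 3: with the enrolment estimate as covariate.** The variance is multiplied by 1 − r², so the half-width is multiplied by √(1 − r²). The last column is the power for a difference of 0.1 SD.

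| r | Variance vs unadjusted | Half-width, SD 450 (SD 400 to 500) | Equivalent unadjusted n per arm, 880/(1 − r²) | Power for 0.1 SD |
|---|---|---|---|---|
| 0 | 100% | 42.0 g (37.4 to 46.7) | 880 | 56% |
| 0.3 | 91% | 40.1 g (35.7 to 44.6) | 967 | 59% |
| 0.4 | 84% | 38.5 g (34.3 to 42.8) | 1048 | 63% |
| 0.5 | 75% | 36.4 g (32.4 to 40.5) | 1173 | 68% |
| 0.6 | 64% | 33.6 g (29.9 to 37.4) | 1375 | 75% |
| 0.7 | 51% | 30.0 g (26.7 to 33.4) | 1725 | 84% |

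**Step 4: effect of the 4000 g exclusion.** Cutting off the upper tail of the covariate lowers r among randomised women. This was simulated with an assumed enrolment estimate of mean 3350 g and SD 400 g, and with variable extra growth averaging 100 g in the expectant arm. A correlation of 0.5, 0.6, 0.7 or 0.8 before exclusion became about 0.45, 0.55, 0.65 or 0.75 in the expectant arm. That drop combines the cut-off with the variable growth. At 0.7 before exclusion, the adjusted variance was about 58% of the unadjusted one, against 51% in the table. Both analyses recovered the same difference of about 100 g, so adjustment changed the precision and not the target.

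**The case against.** The strongest reply is that nothing here is wrong. Under randomisation the unadjusted difference in mean birth weight is unbiased and its error rate is controlled. Covariates for one secondary outcome could be settled in an analysis plan that is not shown. The practical gain may also be small: for a difference of 100 g, the unadjusted analysis gives z = 100/21.5 ≈ 4.7, and a difference of about 60 g, (1.96 + 0.84) × 21.5, already has 80% power.

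Most of this stands and limits the point to an improvement. It does not remove it, because the article does not leave the method open. It names one, and a more precise one is available from data that the trial already obtains.

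A reader might also infer more than the documents support:

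- **That the plan specifies a one-way analysis.** It names ANOVA without listing factors. An unadjusted two-group comparison is the natural reading, but it is an inference.
- **That the trial loses the equivalent of 2.8 times as many women.** That is 1/(1 − r²) at r = 0.8 among randomised women. Nothing in the documents supports so high a value, and the 4000 g exclusion makes it less likely.
- **That mean birth weight is the link in the protocol's causal argument.** The Discussion speaks of the incidence of macrosomia, which concerns the upper tail. A narrower interval for the mean does not estimate that directly.
- **That the change is certain to cost nothing.** The scan is done and used for eligibility, but the article does not show that the value in grams reaches the database. The recruitment form is an additional file and is not shown.

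**Conclusion.** The point holds as a free improvement, not as an error. As written, the plan compares birth weight by a valid but less precise method than its own baseline data allow. With 880 per arm and an assumed SD of 450 g, adjustment would narrow the 95% half-width by about 2 g at r = 0.3, 6 g at r = 0.5 and 12 g at r = 0.7. Both SD and r are assumptions, and the lower and middle part of that range is the safer part to rely on. The documents do not support a claim of bias, or of any effect on the C-section analysis or on the sample size.

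**What to change.** Change the sentence on continuous secondary outcomes so that birth weight is compared by ANCOVA (linear regression) on arm, with these covariates:

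- the enrolment fetal weight estimate in grams;
- gestational age at enrolment, in days;
- centre, which is the stratification factor of the randomisation.

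Report the adjusted mean difference with its 95% confidence interval; the unadjusted difference can stand beside it.

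Do not adjust for gestational age at delivery or for the later scan before induction in the expectant arm. Both arise after randomisation and can be affected by the allocation.

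Before fixing the wording, confirm that the electronic form holds the estimate in grams and not only a yes/no against the 4000 g limit. If it does, the cost is one sentence of analysis text, with no extra visit, scan or participant. If it does not, one field has to be added to the form.

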## Discussion

The aim of the present study is to assess whether induction of labour at term would reduce C-section rate and ameliorate maternal and neonatal outcomes when compared to expectant management in pregnancies affected by GDM.

The main outcome of the study was planned to be a composite of main neonatal morbidity and mortality outcomes possibly related to GDM. The choice of creating a composite outcome derived from the practical impossibility of using shoulder dystocia alone as a single outcome. The rarity of this event would have precluded the possibility of carrying out the study, which would require a very large number of women to obtain significant results. The necessity of including very rare endpoints in a composite outcome in obstetrics research has been recently highlighted [23]. The attempt to include in a unique composite, the neonatal outcomes of interest, has unfortunately failed. In fact this process would have required combining very serious events, such neonatal death or shoulder dystocia, to neonatal hypoglycaemia or hyperbilirubinemia related to much less serious consequences, and for this reason unfeasible.

Therefore the main outcome of the study was decided to be the incidence of C-section among women undergoing induction of labour and those who will be assigned to expectant management with attentive maternal and fetal monitoring. This is a very relevant outcome both for women's health and for health service organizations. Furthermore, C-section rate was the main outcome of the only randomized controlled trial previously carried out on this topic [13].

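### χ² for every categorical secondary outcome with one p<0.05 rule can mislabel sparse tables and leaves about 24 secondary tests open to significance claims (minor)

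*Protocol article*

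**What the plan says.** The analysis paragraph of Methods/Design (after Figure 1) fixes the secondary tests by type of variable only: "the ANOVA technique will be used for continuous variables and χ^2 ^test for categorical". The next sentence sets a single threshold: "Statistically significant differences will be determined by a p-value inferior to 0.05". The paragraph gives no exception for small counts and does not call the secondary comparisons exploratory.

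The Discussion lists the secondary outcomes. They range from common ones (birth weight, episiotomy) to very rare ones (maternal death, perinatal death, birth trauma, maternal intensive care admission). The article is aware of sparsity: it explains why shoulder dystocia could not be the main outcome by saying "The rarity of this event would have precluded the possibility of carrying out the study". It gives no expected rate for any secondary outcome. The opening of the Discussion makes improvement of maternal and neonatal outcomes part of the trial's aim, alongside the caesarean rate.

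The trial is sized on the primary outcome alone: "31% of C-section in the expectant group and 25% in the induction group", "considering α error equal to 5% and 80% power", with 880 women per arm.

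**The concern.** The χ² p-value is a large-sample approximation, and it becomes coarse when expected cell counts fall below 5. The outcomes most likely to be that sparse here are the gravest, and a claim of benefit or harm on deaths would attract attention out of proportion to its evidence. If such a claim rested on a table of four events against none, the choice of test would decide whether it was called significant.

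The same threshold is also applied to every secondary outcome. Because better maternal and neonatal outcomes are a stated aim, an isolated p-value just under 0.05 could be read as an answer to that aim when it is one of some two dozen looks.

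**Working it through.** **Inputs.** From Methods/Design: 880 per arm, 31% versus 25%, α 5%, power 80%, χ², threshold 0.05. From the Discussion: the outcome list. Assumed: event rates for the rare outcomes (range shown), a two-sided test, and χ² without continuity correction.

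**1. The plan's own figure.** n per arm = [1.96·√(2·0.28·0.72) + 0.8416·√(0.31·0.69 + 0.25·0.75)]² / 0.06² = (1.2445 + 0.5332)² / 0.0036 ≈ 878. The stated 880 reproduces, with power 80.1%. The continuity-corrected formula gives 911, so the uncorrected χ² is the natural reading.

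**2. When a table is sparse.** With equal arms the expected count per arm is half the event total s. It is below 5 when s < 10, a pooled rate below 10/1760 = 0.57%.

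**3. Particular tables.** For a versus b events, s = a + b: X² = (a − b)² / [s(1 − s/1760)]. For 4 versus 0: 16 / [4 × (1 − 4/1760)] = 4.009, p = 0.045. Fisher sums the hypergeometric probabilities of tables no more likely than the one observed. Mid-P counts those exactly as likely at half weight.

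| Events | χ² | Mid-P | Fisher |
|---|---|---|---|
| 4 v 0 | 0.045 | 0.062 | 0.125 |
| 5 v 0 | 0.025 | 0.031 | 0.062 |
| 6 v 0 | 0.014 | 0.015 | 0.031 |
| 7 v 1 | 0.034 | 0.039 | 0.070 |

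**4. Error rate given the event total.** This is the null probability that χ² gives p<0.05 once s is known.

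| Total events | 1–3 | 4 | 5 | 6 | 7 | 8 | 9 | 10 | 11 | 12 |
|---|---|---|---|---|---|---|---|---|---|---|
| χ² (%) | 0 | 12.5 | 6.2 | 3.1 | 1.5 | 7.0 | 3.9 | 2.1 | 6.5 | 3.8 |

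Mid-P gives the same values at every total except 4, where it gives 0. Fisher stays below 5% throughout.

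**5. Error rate before the total is known.** Enumerating two binomials of size 880 with a common event rate gives, for χ²:

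| Assumed rate | 0.05% | 0.1% | 0.2% | 0.3% | 0.5% | 1% | 1.4% |
|---|---|---|---|---|---|---|---|
| Type I error (%) | 0.1 | 1.0 | 3.7 | 4.7 | 4.4 | 4.9 | 5.2 |

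Over rates from 0.02% to 5% the maximum is 5.16%, near a rate of 1.4%. Fisher runs from 0.0% to 3.3% over rates of 0.05% to 2%.

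**6. Number of tests.** The Discussion gives 26 outcomes if birth trauma is one item, each Apgar time counts separately and intensive care diagnosis is left out. It gives 24 if mode of delivery (which overlaps the primary) and shoulder manoeuvres are also dropped, and 29 if birth trauma is split into its four components. With 24 tests at 0.05 and no true effects:
- expected number called significant: 24 × 0.05 = 1.2, whatever the correlation;
- chance of at least one, if independent: 1 − 0.95²⁴ = 0.708.

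Both are upper figures here: very rare outcomes reject less often than 5%, and the outcomes are likely to be positively correlated.

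**7. Skewed outcomes.** Simulated type I error of ANOVA (4000 runs, assumed distributions): 3.7% to 4.5% for a mostly zero length of stay, 4.7% for an Apgar-like score, 4.3% for duration among 44 admitted per arm, 2.7% among 5 per arm. None exceeds 5%.

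**The case against.** The strongest reply has three parts.

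First, a reader might infer from step 3 that χ² generally produces false significance for rare harms. It does not. The 12.5%, 6.2%, 7.0% and 6.5% in step 4 are the only totals up to 12 that exceed 5%; the other totals lie well below, and the total is not known in advance. Much of the gap from Fisher reflects Fisher's conservatism, and mid-P departs from χ² only at 4 versus 0. This stands and limits the point to particular tables.

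Second, there is one primary outcome, the rest are labelled secondary, and a condensed article commonly leaves multiplicity and small-count rules to a fuller document. This stands in part: the absence of an adjustment is not a finding. The article does, however, state a test and a significance rule without exception, and a later exact test would depart from that text.

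Third, the outcome list must not be inflated. Uterine rupture appears only as a serious event for the data monitoring committee, and Erb's palsy and intracranial haemorrhage appear as components of birth trauma, not as separately listed comparisons. This stands; deaths are the clear examples.

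A reader might also infer that ANOVA is invalid for Apgar or intensive care stay. Step 7 does not support that, and the article does not say that Apgar will be analysed as continuous.

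**Conclusion.** The point holds as a minor one. The stated rule can label a sparse table significant when exact methods do not, most clearly at 4 versus 0 (0.045 against mid-P 0.062 and Fisher 0.125). It also lets up to about 1.2 of 24 secondary comparisons be declared significant when nothing differs; the 71% chance of at least one is an upper figure that assumes independence.

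It does not show a general inflation of error: over the assumed rates χ² stays at or below about 5.2%. The conclusion rests on those rates, on χ² being uncorrected (with a continuity correction 4 versus 0 gives p = 0.133), and on some outcomes having fewer than 10 events, which is plausible for deaths but not stated. The primary comparison and the 880 per arm are untouched.

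**What to change.** Amend two sentences of the analysis paragraph:

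- For any categorical outcome with an expected cell count below 5, use an exact or mid-P test, named in advance, with an exact confidence interval.
- Confine the 0.05 significance rule to the primary outcome. Report secondary outcomes as estimates with 95% confidence intervals and describe them as exploratory.

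Median and interquartile range for Apgar and intensive care stay would describe them better, but this is optional. A Holm adjustment within a short named family is an alternative if the investigators want formal claims on a few neonatal outcomes; it costs power.

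The change needs no extra recruitment or data. Its price is that fewer secondary results can be called significant. Fisher is conservative at these event rates, while mid-P is less so and will often agree with χ².
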